# The (cost-)effectiveness and cost-utility of a novel integrative care initiative for patients with chronic musculoskeletal pain: the pragmatic trial protocol of Network Pain Rehabilitation Limburg

**DOI:** 10.1186/s12955-020-01569-9

**Published:** 2020-10-01

**Keywords:** Effectiveness, Cost-effectiveness, Cost-utility, Pragmatic trial, Rehabilitation, Chronic musculoskeletal pain, Organization of care, Primary care, Network

## Abstract

**Background:**

Rehabilitation care for patients with chronic musculoskeletal pain (CMP) is not optimally organized. The Network Pain Rehabilitation Limburg 2.0 (NPRL2.0) provides integrated care with a biopsychosocial approach and strives to improve the Quadruple Aim outcomes: pain-related disability of patients with CMP; experiences of care of patients with CMP; meaning in the work of healthcare professionals; and healthcare costs. Firstly, in this study, the effectiveness (with regard to the functioning and participation of patients) of primary care for patients with CMP will be assessed, comparing care organized following the NPRL2.0 procedure with usual care. Secondly, the cost-effectiveness and cost-utility with regard to health-related quality of life and healthcare costs will be assessed. And thirdly, the effect of duration of participation in a local network in primary care will be studied.

**Methods:**

In this pragmatic study, it is expected that two local networks with 105 patients will participate in the prospective cohort study and six local networks with 184 patients in the stepped-wedge based design. Healthcare professionals in the local networks will recruit patients. Inclusion criteria: age ≥ 18 years; having CMP; willing to improve functioning despite pain; and adequate Dutch literacy. Exclusion criteria: pregnancy; and having a treatable medical or psychiatric disease. Patients will complete questionnaires at baseline (T1), 3 months (T2), 6 months (T3), and 9 months (T4). Questionnaires at T1 and T4 will include the Pain Disability Index and Short Form Health Survey. Questionnaires at T1, T2, T3, and T4 will include the EQ-5D-5L, and iMTA Medical Consumption and Productivity Cost Questionnaires. Outcomes will be compared using linear mixed-model analysis and costs will be compared using bootstrapping methods.

**Discussion:**

NPRL2.0 is a multidimensional, complex intervention, executed in daily practice, and therefore needing a pragmatic study design. The current study will assess NPRL2.0 with respect to the Quadruple Aim outcomes: patient health and costs. This will provide more information on the (cost-) effectiveness of the organization of care in a network structure regarding patients with CMP. The other two Quadruple Aim outcomes will be examined alongside this study.

*Trial registration* Netherlands Trial Register: NL7643. https://www.trialregister.nl/trial/7643.

## Background

In Western society, the prevalence of chronic musculoskeletal pain (CMP) is up to 20% in the adult population [1, 2]. CMP, the major cause of pain and disability, includes a diverse range of diagnoses such as nonspecific low back pain, fibromyalgia, complex regional pain syndrome, and nonspecific musculoskeletal pain [2, 3]. Biopsychosocial factors contribute to the development and persistence of pain and the associated perceived disabilities. However, the level of complexity of biomedical and psychosocial factors varies widely between people with CMP. This depends on the biomedical context and meaning of the pain, and on the impact of psychosocial factors, such as depression, anxiety, and social influences, on patients’ functioning [4, 5]. People with CMP often have difficulties in performing a range of daily activities and in maintaining an independent lifestyle. A high intensity of CMP is strongly associated with impaired function and is one of the leading causes of long-term work absenteeism and health-related early retirement, leading to high societal costs [6–10]. Earlier studies have shown that the health-related quality of life and levels of physical activity in people with CMP with a duration of 3–6 months is already low, and work absenteeism is high [1, 11, 12].

Due to high healthcare costs and high work absenteeism, CMP is one of the most expensive health conditions worldwide. In the Netherlands, CMP costs approximately 20 billion euros per year (direct and indirect costs) [11]. Of people with CMP, 60–74% receive treatment and most of these (34–79%) perceive the treatment as inadequate and therefore seek an explanation or solution for their pain problem [1, 13–15]. Earlier research shows that 61% of people with CMP had visited from six to more than 20 healthcare professionals in the year before starting a rehabilitation program [16]. A reason for medical ‘shopping around’ might be the more biomedical-oriented (instead of biopsychosocial-oriented) outlook of the general population, healthcare professionals, and decision-makers, in which explaining and solving the pain remains the ultimate focus [15, 17]. Additionally, healthcare professionals receive inadequate training on the assessment and management of CMP, leading to over- or under-treatment. As a result, the complexity of the patient’s pain problem does not accord with the treatment delivered [17–19]. This highlights the need for adequate (cost-) effective treatment strategies.

Multidisciplinary and interdisciplinary treatments, with a biopsychosocial focus in primary, secondary, and tertiary care, have been shown to be both clinically- and cost-effective for people with CMP [20–26]. In order to overcome the previously-mentioned challenges in rehabilitation care for people with CMP, a National Care Standard for Chronic Pain (NCSCP) was presented in the Netherlands in 2017 [11]. In this standard, a matched and person-centered care approach with multi- and interdisciplinary treatments in an integrated care network was proposed. This integrated care network would provide a shared vision of CMP and its biopsychosocial treatment through guidelines for referral and treatment. Moreover, there would be a focus on the early recognition of subacute pain in order to prevent this from becoming chronic. In line with this, the World Health Organization advises focusing on the stimulation of functioning and participation in the design of (new) rehabilitation care [27, 28].

As an elaboration of the NCSCP, the Network Pain Rehabilitation Limburg 1.0 (NPRL1.0) was developed to provide integrated care with a biopsychosocial approach for people with CMP in order to improve their level of functioning. Its main aim is to deliver the right care, at the right place, by the right person, for the right price, thus accomplishing the Quadruple Aim: improving the functioning and participation of people with CMP; improving the experiences of care of people with CMP; improving the meaning of the work of healthcare professionals; and reducing the healthcare costs of people with CMP [29, 30]. As a first step, a feasibility study was performed in 2017 and 2018 to assess the barriers and facilitators for the development, implementation, and transferability of NPRL1.0 [31]. The main facilitators were that the guidelines provide consistency and transparency in the collaboration of the healthcare professionals and that the iterative, bottom-up implementation strategy fits in with the target population with CMP. However, the current views and knowledge of CMP from the patient’s perspective, as well as from the healthcare perspective, and the current organization of care, are challenges for the implementation of NPRL1.0. The results of this feasibility study were used to adjust NPRL1.0 in areas such as the content of the education days for healthcare professionals, the eHealth application for healthcare professionals and patients, and educational information for patients, in the development of NPRL2.0 [32]. The existing local networks in primary care will participate in a cohort study in NPRL2.0. Additionally, extra local networks in primary care will be recruited. It is expected that healthcare professionals will experience a learning curve, as NPRL2.0 is a multidimensional, complex intervention [33]. Therefore, the long-term results of effectiveness, as well as views and knowledge, regarding CMP must be studied.

In this phase, the Quadruple Aim outcomes from NPRL2.0 will be evaluated. This study will focus on the (long-term) effectiveness, cost-effectiveness, and cost-utility part of the Quadruple Aim for primary care of patients with CMP organized according to NPRL2.0 compared to usual care. The research aims of this study are:To evaluate whether primary care organized according to NPRL2.0 leads to a lower level of pain-related disability in patients with CMP than in patients receiving usual care (effectiveness).To evaluate whether primary care organized according to NPRL2.0 is more cost-effective for the health-related quality of life in patients with CMP than in patients receiving usual care (cost-effectiveness).To evaluate whether primary care organized according to NPRL2.0 leads to higher Quality Adjusted Life Years (QALYs) than in patients receiving usual care (cost-utility analysis).To study the effect of duration of participation and the experience of using biopsychosocial principles in treatment of local networks on (cost)-effectiveness (learning curve).

## Methods

### Study design

In this pragmatic study, the recruiting period will be from April 2019 till March 2020, with follow-ups till December 2020. This study comprises two designs; a prospective cohort study and a stepped-wedge based design.

Two local networks of NPRL1.0 will be enrolled in NPRL2.0. They will receive additional education and information based on the results of the feasibility study of NPRL1.0. In NPRL2.0, they will invite patients to participate in a prospective cohort study.

In the stepped-wedge based design working according to NPRL2.0 will be introduced in three steps in two local primary care networks at the same step (step A, B or C). Local networks that intensively collaborate, due to their geographical location, will be placed together in one step (A, B or C). An independent research assistant will randomly allocate the local networks over the steps. In one local network, at least one therapist, general practitioner (GP), and mental health nurse will participate. Each local network will first recruit patients as controls during a period of care as usual, followed by a 3-month ‘wash-out’ period in which education is given (see Fig. 1). After the wash-out period, a local network will then recruit patients during the intervention period in which NPRL2.0 is the standard of care. According to the stepped-wedge based design, length of control and intervention periods vary in each group: Group A will spend 3 months as control and 5 months with intervention; for Group B, there will be 4 months as control and 4 months with intervention; and Group C will spend 5 months as control and 3 months with intervention. Thus, healthcare professionals in all local networks will recruit patients for participation in both control and intervention groups. Patients will contribute data to either the control group or the intervention group, but not both. A stepped-wedge based design is the most feasible design in this pragmatic study as it has the following advantages: (1) it controls for between-local network variation in daily practice; (2) it gives the opportunity to assess intervention effects in a pre/post comparison across local networks, which increases statistical power; (3) it gives an opportunity to assess learning effects by comparing the results of local networks that transit earlier with those that transit later [34].

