### Sample size

In the prospective cohort, all patients with CMP who visit the two local networks of NPRL1.0 will be invited to participate in the study. Based on the recruitment results of the feasibility study of NPRL1.0, and the number of patients visiting a GP practice, we expect that each local network will also recruit about six patients per month. Therefore, the two local networks from NPRL1.0 together should recruit approximately 132 patients in 11 months. Assuming a dropout rate of 20%, we expect to include approximately 105 patients in this study.

To calculate the desired sample size for the stepped-wedge based design, we used the method described by Woertman et al. [39]. The calculations of the number of patients needed are based on the primary outcome of the cost-utility analysis, the health-related quality of life measured with the 5-level EQ-5D version (EQ-5D-5L). Based on McClure et al., we consider an increase of 0.063 points (SD = 0.013) in 1 year as clinically relevant [40]. In addition, an alpha of 0.05, a power of 80%, a 1:1 ratio between control and intervention groups, and a dropout rate of 30% were assumed. Based on these values and the stepped-wedge based design, a design effect (DEsw) of 0.416 exists, which leads to a required sample size of 184 patients (92 control and 92 intervention). Based on the recruitment results of the feasibility study of NPRL1.0, and the number of patients visiting a GP practice, we expect that each local network will recruit 6 patients per month [32]. Therefore, with a dropout rate of 30% of local networks, six local networks will need to participate.

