### Data analysis

Demographic data (e.g. gender, age, home situation, level of education, nationality, and co-morbidities) will be described overall and separately for the intervention and control groups. Frequencies are to be presented for categorical variables, means and standard deviations (SDs) for normally-distributed continuous variables, and medians and ranges for non-normally-distributed continuous data. The two groups will be tested on differences between characteristics, using the *t*-test for continuous variables and the chi-squared test for categorical variables. If variables differ between the two groups, with *p* ≤ 0.10, they are considered to be potential confounders in further analyses.

Outcomes on questionnaires will be compared using linear mixed-model analysis, to take into account repeated measurements in patients as well as the effects of the clustering of patients within local networks. The fixed part of the model contains treatment group (intervention/control), time, treatment group*time, and cluster (local network). To assess the learning effect in local practices, the time (months) that a local network participates in NPRL2.0 will also be taken into account as a fixed variable. Variables known to be related to the outcome and differing between treatment groups at T1 (*p* ≤ 0.10) will be added to the model. An unstructured covariance structure will be used for repeated measures. Missing values for items in the questionnaires will be handled according to the scoring algorithms of the questionnaires. Missing variables in the follow-up data will not be imputed because linear mixed-model analysis is a flexible method for handling missing data for stepped-wedge and repeated-measures designs (likelihood-based approach). Linear mixed-model analyses will be performed using IBM SPSS Statistics for Windows (version 24.0 or higher, Armonk, NY: IBM Corp.) according to the intention-to-treat principle. Other missing values for non-repeated measures will be handled by multiple imputation, which means that missing values will be predicted using existing values for other variables [66].

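### The steps go live one month apart, so the earlier-versus-later learning comparison spans at most 2 months of experience, and the months term as most naturally read would mostly measure calendar date

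*Protocol article*

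**What the plan says.** Under Study design there are three steps of two networks each. The earliest step has the shortest control window: "Group A will spend 3 months as control and 5 months with intervention". The middle step, B, divides its eight recruiting months evenly. The latest step mirrors the first: "Group C will spend 5 months as control and 3 months with intervention". In every network a 3-month training gap, in which no patients are recruited, separates the two windows. The third listed advantage of the design is that "it gives an opportunity to assess learning effects by comparing the results of local networks that transit earlier with those that transit later". The fourth research aim, at the end of the Background, is the effect of duration of participation on (cost-)effectiveness.

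Under Data analysis, the fixed part of the mixed model holds treatment group, time, their interaction and local network. For learning, "the time (months) that a local network participates in NPRL2.0 will also be taken into account as a fixed variable". The text does not say whether these months are counted at each patient's entry or once per network, and it lists no separate term for calendar date.

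The Discussion expects professionals to need time to absorb the approach, expects no short-term gain in disability or costs, and says that the learning effect will be studied instead.

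**The concern.** An earlier-versus-later comparison can tell experience from date only if, on the same date, some networks have clearly more experience than others. One-month steps give little of that. What is left is the month-to-month change inside each network after go-live, and there experience equals inclusion month minus a constant. Season, a changing mix of recruited patients, or changes in care outside the network would all appear as learning.

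At stake is aim 4. A slope reported as professionals getting better with practice could be a date trend. The point does not concern the estimate for aim 1.

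**Working it through.** **Inputs.** Control/intervention months 3/5, 4/4 and 5/3, a 3-month wash-out, and two networks per step (Study design). Recruitment is uniform: "we expect that each local network will recruit 6 patients per month" (Sample size). Assumed: a common start, since Fig. 1 is not shown. In support, all networks start with a control period, each group's windows sum to 11 months, and the cohort also recruits for 11 months. The document gives no information share or power for the learning term, so there is no stated figure to reproduce.

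**Timeline.** Intervention starts in month 3+3+1 = 7 (A), 4+3+1 = 8 (B) and 5+3+1 = 9 (C). All end in month 11. In any shared month A leads C by 2 months and neighbouring steps differ by 1. Mean experience at entry is 3.0, 2.5 and 2.0 months.

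**Information on the months term** (per patient per network-month; network and group fixed; months counted at entry; time read as T1 to T4). This is the residual sum of squares of experience after the other terms.
- Within networks: 2 × (10 + 5 + 2) = 34.
- Between networks: weights are (control × intervention)/(control + intervention) = 15/8, 16/8, 15/8 = 1.875, 2, 1.875. With means 3, 2.5 and 2 around 2.5, this is 2 × (1.875 × 0.25 + 0 + 1.875 × 0.25) = 1.875.
- Stagger share: 1.875/35.875 = 5.2%. It is about 10% with no network term and about 4 to 9% with random network effects (assumed ICC 0.01 to 0.10).

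**Pass-through of a steady drift d per month.** The gap between mean intervention date and mean control date is 7 months in every group (9−2, 9.5−2.5, 10−3), so the stagger part is free of a linear drift. The within part takes all of it: 34/35.875 = 0.948. Illustration only: a drift of 0.5 PDI points per month gives a false slope of 0.47 per month, or about 1.9 points between a network's first and fifth month (4 × 0.47).

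**Adding one linear date term.** The residual sum of squares of date is 34 (control months) + 34 (intervention months) = 68, and its cross-product with experience is 34. Information: 35.875 − 34²/68 = 18.875. Standard error: √(35.875/18.875) = 1.38 times. The stagger share is still only 1.875/18.875 = 9.9%; the rest comes from extending the control-month date slope into months 7 to 11. For a drift confined to months 7 to 11, the cross-product with experience is 34 − 1.875 = 32.125. Pass-through is 32.125/35.875 = 0.90 without the date term and (32.125 − 17)/18.875 = 0.80 with it.

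**Adding inclusion month as categories.** Information (least squares on the 48 network-months) is 6.4, all from the stagger. Standard error: √(35.875/6.4) = 2.37 times. Pass-through is 0 for any drift common to the networks. The slope stays estimable because months 8 to 11 are shared by at least two steps. Separate linear date slopes for the control and intervention months give information 6.755, a standard error 2.30 times as large, and pass-through 0 for both drifts above.

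**One value per network (5/4/3).** If constant over both periods, it is collinear with the fixed network term. If zero in control months, its information is 2 × (1.875 × 1 + 0 + 1.875 × 1) = 7.5, all between networks.

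**Precision, on an assumed SD of PDI change.** The 95% half-width is 1.96 × SD × √(48/(n × information)). With n = 184 × 0.7 = 129 and SD 13, it is 2.6 PDI points per month unadjusted, 3.6 with the linear term and 6.1 with categories. With n = 288 × 0.7 = 202, from the stated recruitment rate over 48 network-months, it is 2.1, 2.9 and 4.9. Across SD 10 to 16 and both values of n, the range is 1.6 to 3.2 unadjusted and 3.8 to 7.6 with categories.

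**The case against.** The 5% belongs to one reading of the model and not to the design. With one value per network, or with month categories, the stagger supplies all the information. This stands, and the figure must carry its conditions. The conditions are nonetheless close to the text: network is listed in the fixed part, uniform recruitment is the planning assumption, and time appears next to repeated measurements in patients and in an interaction with treatment group. If time meant calendar-month categories, the treatment main effect could not be estimated, because no control month (1 to 5) overlaps an intervention month (7 to 11).

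The design text claims only an opportunity. A reader might infer that the authors will report the slope as an earlier-versus-later contrast. The article does not say so, and the learning section also relies on professionals' experience, knowledge and treatment orientation.

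The two cohort networks from NPRL1.0 offer a longer experience contrast. They do, but it is not randomised and is not the comparison named as the advantage.

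The slope is imprecise in any case and serves the fourth aim. That is true. It limits the weight of the point, but it does not justify attributing a date trend to learning.

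**Conclusion.** The third advantage is weak: on the stated windows and a common start, earlier and later networks differ by at most 2 months of experience at the same date. This sits badly with the Discussion's expectation that effects take time. If months are counted per patient at entry with no calendar term, about 95% of the information is a within-network trend, and a steady drift enters the slope as about 0.95d. If there is one value per network, the term rests entirely on the 2-month spread.

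A reader might go further and infer that learning cannot be separated from date at all. That is not supported: the shared months 8 to 11 allow it, at a wide interval. Nor would a single linear date term settle the matter, since it removes only a drift that is linear over all 11 months. The PDI half-widths and the drift example rest on assumed values; the timeline, shares and pass-through do not. The point is worth acting on, but it is confined to aim 4.

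**What to change.** - State that months of participation are counted at each patient's entry.
- In the aim 4 model only, add inclusion month as categories, or separate linear date slopes for the control and intervention months. Make this the analysis that supports any learning claim.
- Show the unadjusted slope and the slope with one linear date term as supporting analyses. Note that the single linear term leaves about 0.80 of a drift confined to months 7 to 11.
- Call the result learning only if the category-adjusted slope supports it. Otherwise report a trend over the first 3 to 5 months that cannot be separated from date.
- Reword the third advantage to say that the steps give at most 2 months' difference in experience at the same date.

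The cost is one changed secondary model and one sentence. The slope's standard error grows about 2.3 to 2.4 times, so the adjusted analysis may well be inconclusive. The aim 1 model should not take the month categories, because its treatment contrast would no longer be estimable; it stays as planned.
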